### Research questions

The primary research question for family caregivers is:

Does iSupport improve family caregivers’ overall knowledge about dementia?

The secondary research questions for family caregivers are:

Does iSupport improve family caregivers’ caregiving skills required to care for PWD?Does iSupport reduce family caregivers’ stress?Does iSupport improve family caregivers’ mental health?Does iSupport improve family caregivers’ quality of life?Does iSupport improve family caregivers’ relationship with PWD?

The primary research question for formal caregivers is:

Does iSupport improve formal caregivers’ overall knowledge about dementia?

Secondary research questions for formal caregivers are:

Does the impact of iSupport on knowledge about dementia differ between male and female formal caregivers?Does the impact of iSupport on knowledge about dementia vary with the level of caregiving skills of formal caregivers?

In addition, this study aims to capture caregivers’ experience of using iSupport in relation to providing care for PWD, the perceived benefits and challenges of using iSupport, and recommendations for improving the iSupport intervention through qualitative methods.

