### Sample size

The primary objective of this study is to assess the effectiveness of the adapted iSupport manual in enhancing the overall knowledge about dementia and dementia care among both family and formal caregivers. The required sample size estimation was, thus, based on the DKAS. The DKAS has previously been used in multiple studies to assess knowledge and awareness of dementia especially among caregivers of PWD [39,48–50].

A hypothesis test on the mean difference between the pre- and post-intervention DKAS scores will be performed. The hypotheses of interest are as follows:

$$H_{0}:\mu_{d}=0$$

$$H_{1}:\mu_{d}\neq 0$$

where, *μ*_*d*_ is the mean difference of DKAS scores in the population. The sample size was estimated using the following formula:

$$\begin{array}{c} n={\left(\frac{Z_{1-\alpha /2}+Z_{1-\beta }}{\mu_{d}/\sigma_{d}}\right)}^{2} \end{array}$$

here, σd is the standard deviation of mean differences of DKAS scores in the population, $Z_{1-\alpha /2}$ is the value from the standard normal distribution at the significance level α, and $Z_{1-\beta }$ is the value at the power β.

According to a 2016 study by Annear and colleagues (2017) which validated the DKAS among an international cohort of participants, the mean DKAS score was about 34.5 (in a scale of 50; SD_Family_ = 6.8 and SD_Formal_ = 8.4) for both family and formal caregivers [39]. To estimate the sample size, relevant literature that used the DKAS to evaluate knowledge-based interventions related to dementia were consulted. Eccleston and colleagues (2019) evaluated the impact of participating in a Massive Open Online Course (MOOC) on dementia in improving knowledge related to dementia [48]. The course was offered world-wide, however, the majority of the participants (i.e., 74.3%) were from Australia. Their study used DKAS as an outcome indicator as in the proposed study. The published dataset was used to estimate the baseline and end-line DKAS scores [48]. According to the study, the mean difference between overall pre- and post-intervention knowledge scores was about 9.9 (SD = 8.7) and the mean score difference among the participants with exposure to dementia from their family was about 15.0 (SD = 9.0) [48].

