Using these estimates, the sample size was calculated according to the hypotheses of interest at 5% level of significance and 80% power of the test. Since majority of the data represent Australian population, the standard deviation of the mean differences was inflated while estimating the sample sizes. The standard deviation of the mean differences ($\sigma_{d}$) for the family caregivers was multiplied by a factor of three and $\sigma_{d}$ for formal caregivers was multiplied by a factor of two. This conservative approach is expected to help the knowledge assessment adjust for higher variation in DKAS scores. Moreover, the $\sigma_{d}$ for family caregivers was inflated by a higher factor because the family caregivers’ DKAS scores are expected to vary more than that of the formal caregivers. Using the formula, the estimated sample size was 26 for both family and formal caregivers. A 40% attrition rate was assumed since dropouts are comparatively high in these interventions [51]. Incorporating for the attrition, the adjusted sample size for this study would be 44.

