### Data analysis plan

The quantitative results of pre- and post-intervention assessments will be compared. It is hypothesised that statistically significant differences between the pre- and post- outcome indicators will be found. The null hypothesis of zero mean difference will be tested using a two-sample paired t-test for all the outcome indicators. Moreover, multivariable statistical techniques will also be used to control for possible confounders (e.g., gender, age, caregiving skills). Moreover, descriptive and regression analyses will be conducted to identify associations between background and outcome variables. In case of missing data, simple imputation methods will be used. For continuous variables, missing values will be replaced with the mean, while for categorical variables, the mode will be used.

To analyse the qualitative data, content analysis with an inductive approach will be used. The qualitative interviews and FGD recordings will first be transcribed verbatim, ensuring accuracy and completeness. The transcripts will then be translated to English as all interviews will be conducted in the participants’ native language, Bangla. The transcripts will be thoroughly read to identify meaning units, codes, and categories [52]. The process of inductive content analysis includes open coding, creating subcategories, and abstraction to categories. Findings will be discussed back and forth among the authors until they reach a consensus, to increase validity. Transferability will be ensured through a detailed description of the data collection process and a sensitivity to the context in which data will be collected. No software will be used for data analysis.

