### Limitations

The study will employ a non-randomized design and purposive sampling to recruit participants. Furthermore, all formal caregivers included in the study will be exclusively selected from a single agency. These methodological choices may introduce selection bias and limit the generalizability of findings. The absence of a control group, due to financial and logistical constraints, will limit the ability to evaluate the effectiveness of the iSupport intervention in achieving the secondary objectives among family caregivers. Moreover, given the iSupport intervention will be online for most participants, internet connectivity and digital literacy may pose as a barrier to proper access and adherence to the intervention. If this occurs, we will be unable to measure the potential effectiveness of the iSupport manual. Use of the printed manual also presents potential challenges, such as the risk of participants photocopying or retaining the manual, which could compromise the accurate assessment of knowledge retention during the follow-up survey.

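### The plan names no between-group contrast of change for the formal-caregiver gender and skill questions, lists both variables as confounders, and sizes the groups for change within each subgroup

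*Protocol article*

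**What the plan says.** Under Research questions, the protocol article sets two secondary questions for formal caregivers: "Does the impact of iSupport on knowledge about dementia differ between male and female formal caregivers", and "Does the impact of iSupport on knowledge about dementia vary with the level of caregiving skills of formal caregivers". Both are questions of effect modification.

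Under Sample size, the formal-caregiver target goes from 44 to 88 for the gender question (44 per gender) and to 132 for the skill question (44 in each of three employer-assigned levels). The basis is stated: "the sample size was calculated according to the hypotheses of interest at 5% level of significance and 80% power of the test".

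The Data analysis plan names one test: "The null hypothesis of zero mean difference will be tested using a two-sample paired t-test for all the outcome indicators". It adds that "multivariable statistical techniques will also be used to control for possible confounders (e.g., gender, age, caregiving skills") and that "descriptive and regression analyses will be conducted to identify associations between background and outcome variables".

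Under Limitations, the article acknowledges "The absence of a control group, due to financial and logistical constraints".

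**The concern.** Gender and skill level are the variables of interest in the two secondary questions, yet the only role the analysis section gives them by name is that of nuisance variables to be controlled for. A paired t-test of zero change, run overall or inside each subgroup, cannot show that change differs between subgroups. The remaining regression is described too loosely to fill the gap: on raw DKAS scores it would show who scores higher, not who gains more.

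The label also does not fit the design. Everyone receives iSupport and each person is compared with themselves, so a trait that stays the same from baseline to end-line cannot explain the average within-person change.

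At stake are the only two secondary questions for formal caregivers, and the reason for tripling that sample. An analyst who follows the text literally could adjust for the two variables and never report the contrasts.

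**Working it through.** **Inputs (Sample size section).** Mean DKAS change 9.9, SD 8.7 (overall); 15.0, SD 9.0 (participants with family exposure). SD multiplied by 2 for formal caregivers (17.4) and by 3 for family caregivers (27.0). Two-sided 5%, 80% power, so 1.960 + 0.842 = 2.802. Attrition 40%. Applying the overall estimate to formal caregivers is an inference; the text does not say so outright.

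**1. Reproduce the plan's figures.** n = (2.802 × SD / mean)².
- Family: (2.802 × 27.0 / 15.0)² = 25.4, so 26.
- Formal: (2.802 × 17.4 / 9.9)² = 24.2, so 25, against a stated 26.
- Attrition: 26 / 0.6 = 43.3, so 44.
- 2 × 44 = 88 and 3 × 44 = 132.

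The subgroup sizes are thus the one-group paired size, repeated. They power a test of change within each subgroup.

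**2. What those sizes give for a difference in change.** The article states no between-group difference, so 9.9 and 4.95 (all and half of the assumed gain) are assumptions here. With SD 17.4 and 26 completers per group:
- Detectable gender difference at 80% power: 2.802 × 17.4 × √(2/26) = 13.5 points (13.8 with the t distribution).
- Power for a 9.9-point gender difference: 54% (normal), 52% (t). For 4.95 points: about 17%.
- Three levels, evenly spaced means, F test: 42% for a 9.9-point range, 13% for 4.95.
- Completers needed per gender: 2 × (2.802 × 17.4 / 9.9)² = 48.5, so 49 (82 recruited) for 9.9 points; 194 (324 recruited) for 4.95.
- If all 132 recruits split evenly by gender (132 × 0.6 / 2, about 39 completers each), the detectable difference is 11.0 points, still above 9.9.
- With the uninflated SD of 8.7 and 26 per group, it is 6.8 points.

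**3. Does adjustment change the estimated gain?** With complete pairs, each person contributes one baseline and one end-line value, so time is uncorrelated with any fixed covariate and the time effect equals the mean change whether or not the covariate is in the model. A simulation (132 people, 4,000 runs, true gains of 5.0 in one gender and 14.9 in the other) agreed: adding gender and age moved the time effect by less than 10⁻¹³. The 9.9-point difference in gain appeared only in the gender coefficient of a model for change.

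This holds only with complete pairs. As an illustration with assumed dropout of 60% and 20% in two equal-sized genders, the completer mean is (0.4 × 5.0 + 0.8 × 14.9) / 1.2 = 11.6, against (5.0 + 14.9) / 2 = 9.95 for everyone enrolled.

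**4. Illustration: separate subgroup tests compared by significance.** Suppose every subgroup truly gains 9.9 (SD 17.4, 26 completers). Each paired t-test has power 0.796 (noncentral t).
- Two genders disagree: 2 × 0.796 × 0.204 = 32%.
- Three levels not all alike: 1 − 0.796³ − 0.204³ = 49%.

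A direct test of the difference would give a false positive 5% of the time.

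**The case against.** The strongest reply is that the article does plan regression of outcomes on background variables. Gender and level are background variables, and regressing DKAS change on them would be exactly the missing contrast. The Sample size section also states an intent to test both questions, and model detail may sit in an analysis plan that is not shown. This stands in part: it would be wrong to say that the questions will go untested. But the article does not leave these variables open. It names them as confounders, and neither regression sentence mentions change, interaction or a comparison between groups.

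A reader might infer from the 44-per-subgroup sizing that the sponsor will run separate paired t-tests and compare their significance. No sentence says so, and the Sample size section uses comparative language. The 32% and 49% therefore show a risk and are not an error rate of the stated plan.

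A reader might also conclude that covariate adjustment can do nothing useful here. That is too strong. Covariates can add precision. With 40% attrition assumed, standardising to the enrolled mix could correct a completer mean. Gender and level may also confound each other in a model containing both. The argument about fixed traits covers gender and the employer's level only: for family caregivers, caregiving skill is itself an outcome, measured at baseline and end-line.

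Nor does the text support the inference that the main result will be presented as confounder-adjusted. The primary test is the unadjusted paired t-test, and the multivariable work is additional.

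**Conclusion.** The point holds in this form: the protocol article poses two effect-modification questions and sizes the sample for them, but names no analysis that contrasts change between genders or levels, and gives those variables a role that does not answer the questions. Confounding of the mean change by fixed traits does not arise with complete pairs.

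The firmest number is the sizing. 88 and 132 do not provide 80% power for the differences they are said to test: the detectable gender difference is about 13.5 points against an assumed total gain of 9.9, and power for a 9.9-point difference is 52 to 54%. This rests on the SD of 17.4, 26 completers per group, and the use of the overall 9.9 for formal caregivers. With the uninflated SD, the detectable difference falls to 6.8 points. The primary pre-post question is not affected.

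**What to change.** 1. For formal caregivers, specify one model: DKAS change on gender and level, or a mixed model with time, gender, level, time-by-gender and time-by-level.
2. Report the differences in mean change with 95% CIs as the answer to the two secondary questions, and state that significance will not be compared across subgroups.
3. Drop the confounder label for gender and level in that analysis. If covariates are kept elsewhere, state their purpose: precision, attrition, or adjusting gender and level for each other.
4. Restate the Sample size section: 44 per group powers change within a subgroup, not a difference between subgroups. Give the detectable difference and label the two questions exploratory.

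The cost is slightly more analysis work and a less favourable statement of power. No new data are needed: gender is collected at baseline and level is assigned by the employer.

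### The mean-imputation rule does not exempt outcome scores; applied to the planned 40% end-line loss, it would raise the paired t-test's type I error from 5% to about 13%

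*Protocol article*

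**What the plan says.** In the protocol article, the Data analysis plan compares pre- and post-intervention results and states: "The null hypothesis of zero mean difference will be tested using a two-sample paired t-test for all the outcome indicators". The outcome indicators include the DKAS, which is the primary outcome in both caregiver groups, and the family caregivers' secondary scales. The same paragraph then calls for simple imputation when data are missing: "For continuous variables, missing values will be replaced with the mean, while for categorical variables, the mode will be used". It names no exception for outcome scores or for people lost before the end-line survey, and it gives no variance correction.

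The Sample size section expects heavy loss: "A 40% attrition rate was assumed since dropouts are comparatively high in these interventions". It derives 26 per group and raises this to 44. It then asks for 132 formal caregivers, 44 at each of three skill levels.

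**The concern.** A missing end-line score replaced by the mean is a constant that carries no information, yet the t-test counts it as a full observation. This has three consequences.

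- The spread of the differences shrinks and the nominal sample size grows, so the standard error is too small and the false-positive rate exceeds 5%, even when dropout is purely random.
- Each dropout is credited with the completers' average end-line score. If dropouts started lower, the estimated gain is pushed upwards.
- A single grand mean pulls the end-line scores of men and women, and of the three skill levels, towards each other. These are the comparisons for which the formal caregiver sample was enlarged.

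As written, the rule reaches the primary analysis in both groups and every secondary scale. The secondary scales are the more exposed, because a modest change there is easily declared significant when the true error rate is well above 5%.

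**Working it through.** **Inputs from the Sample size section.** Two-sided test; "the sample size was calculated according to the hypotheses of interest at 5% level of significance and 80% power of the test". Mean change 15.0 with SD 9.0 for those with family exposure to dementia, and 9.9 with SD 8.7 overall. I read the first pair as the family caregiver input and the second as the formal caregiver input. The SD "for the family caregivers was multiplied by a factor of three", and "for formal caregivers was multiplied by a factor of two". Attrition is 40%.

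**Reproducing the plan's own figures** with n = ((1.960 + 0.842) × SD / mean change)²:

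- Family: SD 3 × 9.0 = 27.0; n = (2.802 × 27.0/15.0)² = 25.4, so 26, as stated.
- Formal: SD 2 × 8.7 = 17.4; n = (2.802 × 17.4/9.9)² = 24.2, so 25 against 26 stated, a trivial difference.
- Attrition: 26/0.6 = 43.3, so 44, as stated.

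The design therefore expects 26 observed pairs and 18 missing end-lines among 44. At the same rate, 132 gives 132 × 0.6 = 79 observed and 53 missing.

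**Standard error when the end-line mean is imputed.** Let N be enrolled, n observed, σ the common SD and ρ the pre-post correlation (not given in the article). The estimate is the observed end-line mean minus the baseline mean of all N.

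- True variance: σ²[1/n + (1 − 2ρ)/N].
- Variance the t-test reports, on average: approximately σ²[1 + (1 − 2ρ)(n − 1)/(N − 1)]/N.

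At ρ = 0.5 these reduce to σ²/n and σ²/N, so the ratio of reported to true standard error is √(26/44) = 0.769. Simulation puts the average reported standard error about 24% below the true one. The ratio barely moves with ρ. With the article's family SD of 6.8, the values are 1.22 against 1.60 at ρ = 0.124, and 0.89 against 1.17 at ρ = 0.7.

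**Type I error.** Large-sample check: 1.96 × 0.769 = 1.507, with two-sided tail area 13.2%. For 79 of 132: √(79/132) = 0.774; 1.96 × 0.774 = 1.516; tail area 12.9%. Simulation with no true change and dropout completely at random (20,000 runs per setting, ρ from 0 to 0.9) agrees:

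| Analysis | 44 enrolled, 18 missing | 132 enrolled, 53 missing |
|---|---|---|
| End-line mean imputed | 12.4–13.2% | 12.6–13.2% |
| Mean change imputed | 24.7–25.0% | 23.9–24.6% |
| Observed pairs only | 4.7–5.1% | 4.8–5.3% |

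The second row has an exact check. The critical value is multiplied by √[n(n − 1)/(N(N − 1))] = √(650/1892) = 0.586 and referred to a t distribution with 25 degrees of freedom, giving 24.8% (24.1% for 132).

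**Dependence on attrition** (44 enrolled, ρ = 0.5):

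| Missing end-lines | End-line mean imputed | Mean change imputed |
|---|---|---|
| 4 | 6.2% | 7.4% |
| 9 | 7.7% | 11.7% |
| 13 | 9.7% | 16.7% |
| 18 | 12.8% | 24.7% |

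**Bias.** Under end-line-mean imputation the estimate equals the completers' gain plus (18/44) × (completers' minus dropouts' baseline mean). Each point of baseline gap adds 18/44 = 0.41 DKAS points, if dropouts would have gained as much as completers. The article gives no such gap; assumed gaps of 1 to 3 points give 0.4 to 1.2 points.

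**Subgroup differences.** If 40% of each group receives the same grand mean, a true end-line difference δ becomes 0.6δ, a loss of 40%.

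**Non-random dropout.** In one assumed scenario (44 enrolled, lower baseline scorers more likely to leave, no true change), the error was 13–92% with the end-line mean imputed, depending on ρ. With observed pairs only it was 8–41%, so dropping the imputation does not by itself repair informative dropout.

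**The case against.** The strongest defence is that the rule was never meant for people lost to follow-up. It comes after the sentences on confounder adjustment and regression and speaks generally of continuous and categorical variables, which suits stray gaps in covariates. Attrition has its own provision: 44 are enrolled so that 26 remain. A reader might infer that the two sections contradict each other, or that the t-test will certainly be run on 44 or 132 people. The article supports neither. The sections are compatible if over-recruitment absorbs the dropouts and imputation handles the remainder. What stands is that the rule is unrestricted and shares a paragraph with a test of all outcome indicators, so an analyst following it literally would fill in the end-lines.

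A reader might also put the error at 25%. That requires imputing the mean change. The Data collection plan collects a DKAS score at each survey, and the change is derived from these, so the literal reading gives about 13%; 25% is an upper limit under a procedure the article does not describe.

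The 40% is a planning assumption, and the formal caregivers, all employed by one enterprise, may be lost less often. This is fair, and the error falls accordingly.

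It may be said that a feasibility study without a control group need not guard its error rate. Yet the Sample size section describes the primary objective as effectiveness and sizes the study on a hypothesis test, and the analysis plan expects significant differences.

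Finally, bias because dropouts used the manual less is not peculiar to imputation; an analysis of completers shares it.

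**Conclusion.** The point holds conditionally. The rule as written covers outcome scores. If it is applied to missing end-line scores at the planned 40% loss, the paired t-test has a type I error of about 13% rather than 5% in both caregiver groups, with a standard error about 24% too small. This assumes dropout completely at random and hardly depends on the pre-post correlation. The inflation is smaller with less attrition and does not arise from this source if outcome scores are left unimputed. Upward bias in the gain needs the further assumption that dropouts started lower. The 40% shrinkage of gender and level differences needs 40% loss, equal across groups.

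The article fixes this rule in its text, so the point is not a detail left to an analysis plan. It should be corrected before analysis because it reaches the primary outcome. A reader might conclude that the paired t-test must give way to a three-timepoint mixed model as the primary analysis. The defect does not require that: observed pairs restore 5% under random dropout, and the secondary scales are measured at only two timepoints.

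**What to change.** - State that mean/mode imputation applies only to isolated missing baseline covariates, and that DKAS and secondary outcome scores are not mean-imputed.
- Run the planned paired t-test on observed pairs, reporting the number of pairs for each outcome.
- Support it with a likelihood-based repeated-measures model, or multiple imputation, using all available data, since observed pairs alone can mislead when dropout depends on baseline score.
- Add one sensitivity analysis that gives dropouts zero change.

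The cost is analysis wording and a few lines of code. No extra data or participants are needed, because the enrolment target already allows for 26 completers. Confidence intervals will be wider, and p-values less favourable, than under the imputation rule.
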